## 11 ASSESSMENT OF SAFETY

Safety outcome measures are listed in Section 10.1, “Methods and Timing for Assessing, Recording, and Analyzing Appropriate Outcome Measures”. Specifications of safety outcomes are described here.

### 11.1 Specification of Safety Parameters

Safety is a primary study outcome measure. Specifications of safety parameters are listed in detail below.

- To evaluate the safety of these skin test antigens in healthy non-contacts, with a particular interest in assessing whether, and to what degree, individuals are sensitized to the antigens (study Stages A and B)
- To evaluate the safety of these skin test antigens in leprosy patients and contacts of leprosy patients (study Stage C)

### 11.2 Methods and Timing for Assessing, Recording, and Analyzing Safety Parameters

Refer to Section 2.1.2, “Leprosy Skin Test Antigens, 1919-today”, for relevant information and references on the history and safety of prior leprosy skin test antigens. The primary source of risk information for this investigational product is the Investigator’s Brochure.

#### 11.2.1 Adverse Events, Reactogenicity and Serious Adverse Events

The Principal Investigator is responsible for reporting all AEs that are observed or reported during the study, regardless of their relationship to study product.

##### 11.2.1.1 Definitions

###### 11.2.1.1.1 Adverse Event (AE)

An AE is any untoward medical occurrence in a patient or clinical investigation subject to whom a pharmaceutical product has been administered, and that does not necessarily have a causal relationship with this treatment. An AE can therefore be

any unfavorable and unintended sign (including an abnormal laboratory finding), symptom, or disease temporally associated with the use of a medicinal (investigational) product, whether or not in association to the medicinal (investigational) product, within a specified period of time. The occurrence of an adverse event may come to the attention of study personnel during study visits and interviews or by a study recipient presenting for medical care.

All adverse events must be graded for intensity and relationship to study product.

#### **11.2.1.1.2 Serious Adverse Event (SAE)**

An SAE is any untoward medical occurrence within a specified period of time that at any dose:

- Results in death.
- Is life-threatening. Any adverse therapy experience that places the subject, in the view of the investigator, at immediate risk of death from the reaction as it occurred (i.e., it does not include a reaction that, had it occurred in a more serious form, might have caused death).
- Requires in-patient hospitalization or prolongation of existing hospitalization.
- Results in persistent or significant disability or incapacity.
- Is a congenital anomaly/birth defect.
- An event that required intervention to prevent permanent impairment or damage.

Important medical events that do not result in death, are not life-threatening, or do not require hospitalization may be considered serious adverse events when, based upon appropriate medical judgment, they might jeopardize the subject and might require medical or surgical intervention to prevent one of the outcomes listed above.

#### **11.2.1.1.3 Reactogenicity**

Reactogenicity events are adverse events that are common and reasonably expected for the intervention/investigational product being studied. Reactogenicity events will be collected at the time of injection site assessment, observed during study visits.

### **11.2.2 Management of Possible Adverse Events**

Adverse events will be managed according to standard care of the study medical staff or primary care physician.

### **11.2.3 Management of Possible Serious Adverse Events**

Serious adverse events will be managed according to standard care of the study medical staff or primary care physician.

## **11.3 Reporting Procedures**

### **11.3.1 Adverse Events**

Adverse Events including local and systemic reactions not meeting the criteria for “serious adverse events” should be captured on the appropriate case report form. Information to be collected includes event description, time of onset, investigator assessment of severity, relationship to study product, time of resolution of the event, seriousness, and outcome. All adverse events occurring while on study must be documented appropriately regardless of relationship. All AEs will be followed to stabilization, if they do not resolve. An event is reportable as associated with the product if the possibility of a relationship of the product to the event cannot be ruled out.

Any medical condition that is present at the time that the subject is screened should be considered as baseline and not reported as an AE. However, if it deteriorates at any time during the study it should be recorded as an AE.

**Not Associated** -the AE is completely independent of study product administration; and/or evidence exists that the event is definitely related to another etiology.

### 11.3.3 Reporting of Pregnancy

Pregnancy tests will be performed during study screening. Pregnancies that are reported by the subject during study participation will be reported as adverse events and the volunteer will be referred to their physician following standard referral procedures.

## 11.4 Halting Rules

Safety findings that would temporarily suspend enrollment and/or study intervention until an *ad hoc* safety review meeting is convened by phone or e-mail with the DMID PO, the ISM and/or the SMC would include:

- Any SAE deemed associated to the skin test antigens
- AEs occurring that, in the opinion of the investigator and ISM may warrant review by the SMC
- Any death, whether related or not

The DMID PO, with input from the ISM and/or the SMC, will determine whether the study should continue per protocol, proceed with caution, be further investigated, be discontinued, or be modified and then continued. Suspension of enrollment (for a particular group or for the entire study) is another potential outcome of these recommendations. Recommendations by the DMID PO will then be submitted to DMID, NHRC, CSU IRB, and the FDA.

***Ad Hoc Meetings of SMC:*** The SMC may convene an *ad hoc* meeting to discuss any issue of safety raised by an investigator, the sponsor, or a member of the SMC. At the discretion of the investigators, the sponsors, and SMC members, a non-serious adverse event that is either associated with the product, or does not meet the stopping rules criteria may be considered as a trigger for an *ad hoc* SMC meeting to assess the safety of the product, without resulting in halting the enrollment of the trial.

## **12 CLINICAL MONITORING STRUCTURE**

Site Monitoring will be conducted to ensure that human subject protection, study procedures, laboratory procedures, study intervention administration, and data collection processes are of high quality and meet sponsor, CGP/ICH, and regulatory guidelines, and that the study is conducted in accordance with the protocol and sponsor SOPs. DMID, the sponsoring agency, or its designee will conduct site monitoring visits either on-site or off-site as detailed in the monitoring plan or in the Manual of Operations.

## 13 STATISTICAL CONSIDERATIONS

### 13.1 Overview and Study Objectives

#### 13.1.1 Scientific Rationale

The overall objective is to evaluate two new leprosy skin test antigens as diagnostic/epidemiological tools designed to measure the extent of leprosy infection in individuals and communities living in leprosy endemic areas.

#### 13.1.2 Objectives

##### Stage A

- Primary objective:  
To evaluate the safety of the two leprosy skin test antigens in a small number of healthy individuals without known exposure to clinical leprosy or tuberculosis, living in a region endemic for leprosy.

##### Stage B

- Primary objective:  
To evaluate the safety of the two leprosy skin test antigens in larger numbers of healthy individuals without known exposure to clinical leprosy or tuberculosis, living in a region endemic for leprosy.
- Secondary objectives:
  - To compare responses to the leprosy skin test antigens to those of PPD/tuberculin, in order to determine if there is differentiation between the two in this population with presumed exposure to indigenous *Mycobacterium tuberculosis*, other indigenous mycobacteria, and in some cases, subjected to BCG vaccination.
  - To combine data on skin test responses to the leprosy skin test antigens and to PPD/tuberculin, with data from an equivalent group in Stage C, to arrive at a valid definition of a positive response, versus a negative response (i.e. “cut-off” point).

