Other campuses/hospitals may also be selected to participate. All subjects entering the study will be asked to read (or have read to them) and sign a detailed consent form. Of these 160 individuals, 80 will be cases of leprosy from the AH (40 BL/LL and 40 BT/TT leprosy patients), 40 will be healthy contacts of BL/LL leprosy patients, and 40 will be tuberculosis patients recruited from the Patan Hospital TB clinics. Participants other than TB patients will be free of intercurrent tuberculosis, and will not have taken immunosuppressive therapy for at least 4 weeks prior to study participation. TB patients must have completed the intensive phase of anti-tuberculosis therapy and taking anti-tuberculosis medicines at the time of testing. Volunteers will be contacted directly and invited to participate after an informational talk about the study given by the investigators approximately 1-2 weeks before study initiation at the listed campuses or at hospital wards, or in the case of tuberculosis patients, given during the weekly clinic or hospital ward visits.

Each volunteer who agrees to enter the study and provides informed consent will be assigned a subject screening number. This number and the name of the volunteer will be recorded in a log kept by the Study Coordinator (SC). In order to protect the privacy of each participant, only their subject number will be used on all CRFs and data analysis reports.

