Stage C: Upon completion of Stage B, and with approval from DMID, NHRC, and CSU IRB (no sooner than 4 days after the final reading of Stage B), 160 Nepali individuals (including expatriates from India) will be studied in Stage C. This stage is broken down into two parts: Stage C-1 and Stage C-1b, in which 80 subjects from four high risk groups will be studied in each Stage to measure the safety and/or reactivity of the antigens at the high dose (1.0µg) and low dose (0.1µg), respectively. In addition, each subject will provide a 5ml tube of heparinized blood for the laboratory personnel to perform a QuantiFERON-CMI test using leprosy antigens and a 3ml serum separator tube of blood to perform the Rapid PGL-I Antibody Test.

Stage C-1: In order to assess the likelihood of large ulcerating reactions in subjects in higher risk groups, we will first assess the safety of the injections in 80 subjects (20 from each group, except healthy non-contacts) before enrolling any additional subjects. Each individual will receive three 100µl injections (one of each high dose from each test antigen, and one of 2TU Tuberculin/PPD). The injections will be administered as previously described for Stage A, with one exception: the test sites will be at 1.5 inches, and 3.5 inches below the bend of the elbow on one arm and 3.5 inches below the bend of the elbow on the other arm, allowing a total of three injection sites. Each subject will be

randomly assigned one template for antigen administration (see Section 6, “Randomization/Enrollment/ Blinding Procedures”). Safety data will be collected and reviewed by the SMC, and their report will be forwarded to DMID, NHRC, and CSU IRB.

Stage C-1b: To further assess the reactivity of the skin test antigens, the low dose of each antigen will be administered to 80 subjects (20 from each group, except healthy non-contacts) exactly as stated in Stage C-1.

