## 13.2 Study Population

All subjects for Stages A, B, and C will be Nepali nationals (including expatriates from India), between the ages of 18 and 60 years, weighing greater than 30 Kg (female) or 38 Kg (male). Healthy, non-leprosy exposed subjects and tuberculosis patients will serve as the negative control group. Healthy leprosy exposed contacts and BT/TT leprosy patients will serve as positive control groups, and BL/LL leprosy patients will serve as concurrent controls.

The skin test reactions will vary among the groups participating in this study. It is expected that the non-contacts and BL/LL leprosy cases along with the tuberculosis patients will have smaller or negative indurations at all leprosy skin test sites. The tuberculosis patients will react with a large induration at the PPD/tuberculin site, and may react with an induration less than 10 mm at the other sites. Healthy contacts of leprosy patients and BT/TT leprosy patients are expected to have larger indurations at *M. leprae*-derived antigen sites, and a variable reaction at the site of the PPD/Tuberculin. Data collected from skin test reactions from these five groups will allow study objectives to be met.

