### 13.3 Study Design

This is a prospective study where the participants all receive the same set of antigens, but are randomized to receive them in different patterns, that is, according to different “templates”. The participants do not know which template is used and the readers, or evaluators are also blinded to the pattern of antigen delivery. Stages A and B randomized participants to only a single study antigen, at two doses for each volunteer, plus PPD and saline. Schemas for stages A plus B and C follow.

[figure not shown]

Volunteers in stage C-1 will receive both leprosy skin test antigens at the high dose of 1µg per 100µl and PPD at 2TU, while volunteers from stage C-1b will receive the same antigens at the low dose of 0.1µg per 100µl and PPD at 2TU. Since three test sites are required as compared to four in Stage A and B, they will be reassigned (2 sites on the first arm and one on the second arm), and administration templates will be randomized to different administration patterns. For Stage C-1 and C-1b, there will be 20 subjects from each study group, except healthy non-contacts (contacts of leprosy patients; BT/TT and BL/LL leprosy patients; and, tuberculosis patients).

[figure not shown]

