### 13.6.2 Leprosy Detection/Diagnosis

The utility of a medical diagnostic test is often expressed in terms of the receiver operating characteristic (ROC) for the test (37). The ROC is a plot of the relationship between the false positive rate (FPR), or 1-specificity, and the true positive rate (TPR), or sensitivity. Given a pair of individuals, one with and one without the medical condition of interest, the area under the ROC curve (AUC) is equal to the probability that the test will correctly discriminate between this pair. This study will be the first one using these test antigens in volunteers with the condition of interest making it difficult to establish a hypothesis concerning the AUC.

The study design provides for a variety of possible subset analyses for a given dose of each antigen. Nine combinations of volunteers expected to be non-reactive and reactive respectively are listed in the following table. This is not a definitive Phase III trial, although it has some characteristics in that specificity/sensitivity are considered in the analysis, thus adjustments for multiple comparisons are not considered here. The multiple comparison possibility will be considered at the time of actual data analysis.

Although the observational unit in this study is an individual injection site, the experimental unit is subject. Since subjects in C-1 will receive the higher dose of antigen and C-1b subjects the lower dose, results from C-1 and C-1b will not be combined to construct the ROC curve or to estimate the sensitivity/specificity of the antigens. However, independently, C-1 or C-1b will be used construct the ROC curve and estimate the sensitivity and specificity for each dose of the antigen separately. The estimates and sample sizes in the remainder of this section reflect this.

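### The cut-off objective in 13.1.2 relies on a Stage C group that is not enrolled, and 13.6.2, read literally, does not use the Stage A/B non-contacts as the specificity reference

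*Protocol*

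**What the plan says.** **Cut-off.** Protocol 13.1.2 (Stage B, secondary objectives) combines Stage B skin test data "with data from an equivalent group in Stage C, to arrive at a valid definition of a positive response". The Stage B population is healthy people with no known exposure to leprosy or TB.

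**Who is in Stage C.** Section 5.1.4: "Of these 160 individuals, 80 will be cases of leprosy from the AH (40 BL/LL and 40 BT/TT leprosy patients"; the other 80 are 40 healthy contacts of BL/LL patients and 40 TB patients. Section 13.3, for both C-1 and C-1b: "there will be 20 subjects from each study group, except healthy non-contacts". Section 8.2.2 makes the same exception.

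**Roles of the groups.** Section 13.2: "Healthy, non-leprosy exposed subjects and tuberculosis patients will serve as the negative control group". It continues: "Healthy leprosy exposed contacts and BT/TT leprosy patients will serve as positive control groups, and BL/LL leprosy patients will serve as concurrent controls". Section 3.4 pools the Stage A and B non-contacts and compares them with every Stage C group. Section 4.1 uses non-contacts as the baseline for the cut-off. Section 10.1 compares the 100 non-contacts with the Stage C groups and links the comparison of leprosy patients with non-exposed volunteers to the sensitivity and specificity estimates. The primary objective in 3.1 compares positive reactors in healthy subjects with those in the other groups.

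**Section 13.6.2.** Because C-1 and C-1b use different doses they are not pooled, and "C-1 or C-1b will be used construct the ROC curve and estimate the sensitivity and specificity for each dose of the antigen separately". The section adds that its remaining sample sizes follow from this. It then announces: "Nine combinations of volunteers expected to be non-reactive and reactive respectively are listed in the following table". The table as legible has two expected-negative rows (BL/LL; BL/LL plus TB) and three expected-positive columns. The precision table gives n = 36 and n = 72 only.

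**The concern.** The only healthy people in Stage C are household contacts, whom 13.2 places on the expected-positive side. No Stage C group is therefore equivalent to the Stage B non-contacts, and the stated route to the cut-off does not exist.

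Section 13.6.2 then bears on the primary objective of estimating specificity for *M. leprae* infection. Followed literally, it would estimate specificity without healthy non-exposed people: in the legible rows the expected negatives are all BL/LL patients, or half BL/LL and half TB patients. BL/LL patients have leprosy. Section 13.2 explains their weak response by anergy, so a non-reaction in that group does not show that the test is specific for infection. Section 2.2 makes further studies depend on sensitivity and specificity of about 90% or more, so the denominator of specificity should be fixed without ambiguity.

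**Working it through.** **1. Healthy non-contacts in Stage C.** From 5.1.4: 160 − 80 leprosy − 40 contacts − 40 TB = 0. Section 5.1 agrees: it gives 100 non-contacts in the whole trial, and Stages A and B use 10 + 90 = 100.

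**2. Available reference.** Each non-contact received one leprosy antigen at both doses (5.1.4, 8.2.2). Reading times are in 4.5.
- At 69–75 h: 5 + 45 = 50 per antigen at each dose; after the protocol's 10% loss, 50 × 0.9 = 45.
- At day 6–8 (Stage B only): 45; after loss 45 × 0.9 = 40.5, about 40.

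**3. Stage C groups per dose.** 20 × 0.9 = 18 each. The 36 and 72 in 13.6.2 are two and four times this figure, so they count both doses together although the same section says the doses are analysed separately.

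**4. Is the omission in 13.6.2 established?** Two rows by three columns is six combinations; nine are announced. A row may have been lost in reading the PDF.
- The section calls 72 and 72 its largest sample. On the table's own counting, non-contacts plus TB would be 45 + 36 = 81, above 72, so that row was not there.
- Non-contacts alone would give 45 against 36, 36 and 72. That fits between the quoted extremes, and three rows by three columns is nine. A TB-only row (36) fits equally well.
- So the 72-and-72 statement does not show that non-contacts were left out. The support is the literal wording that takes specificity from C-1 or C-1b, and a precision table without n = 45.

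**5. Precision.** Half-width = 1.96 × √(p(1 − p)/n). Check against the protocol's table: p = 0.5, n = 36 gives 0.163 (stated 0.16); p = 0.9, n = 72 gives 0.069 (stated 0.07). At p = 0.90:

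| Expected negatives, per dose after loss | n | Half-width |
|---|---|---|
| BL/LL | 18 | 0.139 |
| BL/LL + TB | 36 | 0.098 |
| Non-contacts, day 6–8 | 40 | 0.093 |
| Non-contacts, 69–75 h | 45 | 0.088 |
| Non-contacts + TB (45 + 18) | 63 | 0.074 |

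**6. Detectable AUC differences.** The protocol states 0.186 (36 and 36, null 0.5) and 0.101 (72 and 72, null 0.75), two-sided 5%, 80% power. The Hanley–McNeil variance gives 0.187 and 0.106; the Obuchowski binormal variance gives 0.184 and 0.115. Neither reproduces both figures, so no new AUC values are offered for the added comparisons.

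**The case against.** The strongest reply is that 13.6.2 is a sample-size illustration. It speaks of possible subset analyses and says its values only indicate power. Section 13.9.3, the operative analysis text, restricts the reference group in no way, and 13.9 allows groups expected to respond alike to be combined. The sentence about C-1 or C-1b explains why doses are not pooled; it does not say that only those stages may be used. This largely stands: the intended reference can be recovered from the rest of the protocol. It does not help 13.1.2, whose named group does not exist, and it leaves 13.6.2 at odds with 3.4, 10.1 and 13.2 for anyone who follows its wording.

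A reader might infer that the 72-and-72 statement proves the non-contacts were left out. It does not: a row of 45 non-contacts is compatible with it.

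A reader might also infer that treating BL/LL patients as low reactors is itself an error. It is not: sections 4, 8.2.2 and 13.2 all expect small or negative reactions in that group. The objection is only to making them the main denominator for specificity for infection.

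Finally, most of the contrast between n = 18 and the larger samples comes from the pooling of doses in the table, which is a separate fault. The gain that belongs to this point starts from n = 36.

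**Conclusion.** The point holds on two levels. It is certain that the cut-off objective in 13.1.2 cannot be carried out as worded. It is supported, but only on the literal wording of 13.6.2 and its n = 36 and 72 precision table, that the section leaves the Stage A/B non-contacts out of the specificity and ROC reference, against 3.1, 3.4, 4.1, 10.1 and 13.2.

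The precision effect is modest: a half-width of 0.098 (n = 36) against 0.088 (n = 45) or 0.074 (n = 63), assuming 10% loss and an observed specificity of 0.90. A reader might infer that the trial lacks healthy controls, or that specificity will be biased in a known direction. The documents support neither: the controls were enrolled in Stages A and B, and nothing in the protocol gives the direction or size of any shift in cut-off, sensitivity or specificity. The change should be made, because it settles which people define a negative result for a primary objective.

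**What to change.** **13.1.2.** Replace the equivalent-group phrase with the pooled Stage A/B non-contacts, for each leprosy antigen at the matching dose (50 at 69–75 h; 45, Stage B only, at day 6–8; before losses), set against the named Stage C groups. Do not pool PPD across stages: 9.1.2 gives 5 TU Tubersol in A and B and 2 TU RT 23 in C.

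**13.6.2.** State that specificity and the ROC curves use this reference at the same dose, with TB and BL/LL patients as separate comparisons. Put every row on the per-dose basis after 10% loss, against BT/TT, contacts, and both:
- BL/LL: 18 and 18, 18 and 18, 18 and 36
- BL/LL plus TB: 36 and 18, 36 and 18, 36 and 36
- non-contacts: 45 and 18, 45 and 18, 45 and 36
- non-contacts plus TB: 63 and 18, 63 and 18, 63 and 36

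These four rows make 4 × 3 = 12 combinations; correct the announced nine to match whatever rows the final table holds. Give the precision table for n = 18, 36, 45 and 63, and rerun the detectable AUC differences for the same rows.

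**Cost.** One phrase, one sentence, a rebuilt table, a revised precision table and an AUC rerun. No enrolment: 13.7 records Stages A and B as complete.

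**Limits to state.** The reference is non-concurrent and comes largely from other sites. It was read at 69–75 h against day 2–4 in Stage C. Each non-contact received only one antigen, so a paired comparison of the two antigens is available only within Stage C.
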